### 8.5.1 Emergency procedure for unblinding

Not applicable due to the open-label study design.

### 8.5.2 Unblinding at the end of the study

Not applicable due to the open-label study design.

## 8.6 Benefit and risk assessment

As this study is primarily designed for the assessment of safety, tolerability and feasibility of a single dose of neoadjuvant ipilimumab and following 3 cycles of nivolumab in combination with standard neoadjuvant CRT in rectal cancer, there is no explicit benefit for the individual participant. Other interventions, such as blood drawing, tumor biopsies, computed tomography (CT), magnetic resonance imaging (MRI), positron-emission tomography (PET), neoadjuvant CRT, following surgical resection are standard care of treatment for rectal cancer patients. However, it is expected that patients within the treatment arm are going to have a major benefit in terms of pathological response and consequently clinical outcome.

## 8.7 Study procedures

### 8.7.1 General rules for trial procedures

- All study measures like blood sampling and measurements (vital parameters, ECG, *etc.*) have to be documented with date (dd.mm.yyyy).
- In case several study procedures are scheduled at the same time point, there is no specific sequence that should be followed.
- The dates of all procedures should be according to the protocol. The time margins mentioned in the study flow chart are admissible. If for any reason, a study procedure is not performed within scheduled margins a protocol deviation should be noted, and the procedure should be performed as soon as possible or as adequate.
- If it is necessary for organizational reasons, it is admissible to perform procedures which are scheduled for one visit at two different time points. Allowed time margins should thereby not be exceeded.

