### 5.2 Study rationale

The concept of combining radiotherapy with ICI is currently investigated in a variety of solid cancers including lung cancer, melanoma and head and neck cancer, as preclinical data has shown some promising synergistic effects [13]–[15]. First clinical results of small patient series support this hypothesis [16]. The safety aspect of this combination has already been documented for liver metastases of melanoma without grade 4 toxicities. Furthermore, ICI has also been combined with chemotherapy, which showed limited toxicity [17]. Yet, little data is known for the combination of CRT with sequential ICI.

Dual checkpoint therapy has been investigated in humans and appears to have additive or synergistic effects [18]–[20]. Usually, dual ICI is given at the same time. However preclinical and experimental data indicate that anti-CTLA-4 deplete regulatory T (Treg) cells and might have a priming effect for cytotoxic T cells following anti-PD-1 treatment to counterattack T cell exhaustion. Thus, the sequential blockade of the CTLA-4 and PD-1 might have an additional advantage to simultaneously inhibition.

Most recent it was shown that immunomodulating therapy applied before surgical resection are highly beneficial, which increase the recurrent-free survival (RFS) [21]–[25]. This finding suggests that systemic immune stimulation appear to purge occult micrometastases. Thus, the highest biological effects of immunotherapy might be in the early phase to tumor treatment, which focuses on the enhancement of cure rates. This provides the rationale to combine ICI with currently applied standard neoadjuvant therapies in solid tumors.

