### 6.2 Secondary objectives

- Radiographic response determined by magnetic resonance imaging-assessed tumor regression grade (mrTRG) [28]:
  - mrTRG 1 (no evidence of ever treated tumor)
  - mrTRG 2 (good response: dense fibrosis no obvious residual tumor)
  - mrTRG 3 (moderate response: >50% fibrosis or mucin & visible intermediate signal)
  - mrTRG 4 (slight response: little areas of fibrosis or mucin, but mostly tumor)
  - mrTRG 5 (no response)
- Pathological therapy response determined by tumor regression grade (TRG) [29]–[32] and the latest American Joint Committee on Cancer/International Union Against Cancer-Tumor Node Metastasis (AJCC/UICC-TNM) tumor stage [33].  
TRG according to Dworak *et al.* [32]:
  - TRG 0 (no regression)
  - TRG 1 (predominantly tumor with significant fibrosis and/or vasculopathy)
  - TRG 2 (predominantly fibrosis with scattered tumor cells)
  - TRG 3 (only scattered tumor cells in the space of fibrosis with/without acellular mucin)
  - TRG 4 (no vital tumor cells detectable)
- Correlate genomic information (*i.e.* MSI, KRAS, BRAF, TP53, PTEN, PIK3CA, TMB, *etc.*) with pathological and radiographic therapy response.
- Correlate genomic, transcriptomic, epigenomic and/or proteomic pattern of liquid biopsies (serum, plasma, PBMCs) taken on day -21 to -1, 7, 14, 28, 42, before surgery and at the EOSV with therapy response and clinical outcome.
- Correlate genomic, transcriptomic, epigenomic and/or proteomic pattern of tumor biopsies taken on day -21 to -1, 14 and 28 with therapy response and clinical outcome.
- Correlate immune infiltrate of resected specimen with therapy response

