### 8.2.3 Dosage and administration

**Initial dose:** Ipilimumab 1 mg/kg on day 7 during standard neoadjuvant CRT

**Maintenance dose:** N.A.

**Route of administration:** IV over 30 minutes

**Duration:** single dose

**Initial dose:** Nivolumab 3 mg/kg on day 14 during standard neoadjuvant CRT

**Maintenance dose:** 3 mg/kg

**Route of administration:** IV over 30 minutes

**Duration:** given every 2 weeks until day 42 (3 cycles in total)

**Initial dose:** Capecitabine 1650 mg/m^2/d given as two equal doses per day concurrent with standard neoadjuvant CRT

**Maintenance dose:** 1650 mg/m^2/d given as two equal doses per day

**Route of administration:** PO

**Duration:** given concurrent with standard neoadjuvant CRT over 25 working days

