### 8.2.5 Study drug interruption or discontinuation

The Investigator must temporarily interrupt or permanently discontinue the study drug according to the specifications in the drug specific SmPC.

The reason for study drug interruption or premature permanent discontinuation must be documented in the eCRF.

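### Section 8.7.1 sets no order for same-visit procedures and requires only a date, so research samples taken on infusion days may mix pre- and post-infusion states

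*Protocol*

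**What the plan says.** Protocol section 8.7.1 gives the general rules for trial procedures. Three of them bear on this point.

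- Order: "In case several study procedures are scheduled at the same time point, there is no specific sequence that should be followed".
- Record: study measures such as blood sampling "have to be documented with date (dd.mm.yyyy", that is, by day, month and year. No clock time is required.
- Splitting: for organizational reasons "it is admissible to perform procedures which are scheduled for one visit at two different time points", within the allowed margins. On those margins the section says: "The time margins mentioned in the study flow chart are admissible".

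Section 8.2.3 puts the single ipilimumab dose on day 7. It starts nivolumab on day 14 ("Nivolumab 3 mg/kg on day 14 during standard neoadjuvant CRT") and repeats it every two weeks up to day 42, so on days 14, 28 and 42.

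Section 8.7.6 schedules on-treatment liquid biopsies on days 7, 14, 28 and 42. Section 8.7.5 schedules on-treatment tumor biopsies on days 14 and 28. One of the secondary objectives in section 6.2 is to correlate omics patterns of "tumor biopsies taken on day -21 to -1, 14 and 28 with therapy response and clinical outcome", and a parallel objective covers the liquid biopsies. Section 8.7.5 adds that these analyses are longitudinal and that samples are compared between the two arms.

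**The concern.** The sampling days and the infusion days coincide, and section 8.7.1 leaves their order open. One patient's day 14 blood may be drawn before the first nivolumab infusion and the next patient's after it. Both would be labelled day 14, and the required date would be the same. Serum, plasma or cells collected after an antibody infusion represent a different exposure state from those collected before it. The problem arises only in the treatment arm, because controls receive no infusion.

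At stake is how well the day-labelled biomarker data can be interpreted. The regimen's rationale in section 5.2 is that "anti-CTLA-4 deplete regulatory T (Treg) cells and might have a priming effect for cytotoxic T cells following anti-PD-1 treatment". The samples that could describe the state between the two drugs are those of day 14, and the state during CRT before either drug is captured in the treatment arm only on day 7. The trial is multicenter, so local habits may differ. An analysis plan written later cannot restore an order that was not set or a time that was not recorded.

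**Working it through.** The plan gives no figure for this point. The check sets the infusion schedule against the sampling schedule and counts the doses received at each sample under either order.

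**Inputs.** Infusion days come from section 8.2.3 and Table 4: ipilimumab at visit 3 (day 7), nivolumab at visits 4, 6 and 8 (days 14, 28 and 42). Sampling days come from sections 8.7.5 and 8.7.6 and Table 4. The planned treatment arm is 50 patients (synopsis).

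**Overlap and cumulative doses in the treatment arm.**

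| Visit (day) | Infusion | Research samples | Doses if sampled before | Doses if sampled after |
|---|---|---|---|---|
| 3 (7) | ipilimumab | liquid | none | 1 ipilimumab |
| 4 (14) | nivolumab | liquid, tumor | 1 ipilimumab | 1 ipilimumab, 1 nivolumab |
| 6 (28) | nivolumab | liquid, tumor | 1 ipilimumab, 1 nivolumab | 1 ipilimumab, 2 nivolumab |
| 8 (42) | nivolumab | liquid | 1 ipilimumab, 2 nivolumab | 1 ipilimumab, 3 nivolumab |

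All four liquid biopsy days and both tumor biopsy days are ambiguous by exactly one dose.

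**Where the ambiguity changes the kind of exposure.** At day 7 it decides whether any immunotherapy has been given, and at day 14 whether nivolumab has been given. At days 28 and 42 both drugs have been given in either order, and only the number of nivolumab doses is uncertain.

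**Upper bounds.**

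- Liquid samples at days 7 and 14: 50 × 2 = 100.
- Tumor biopsies at day 14: 50 × 1 = 50.
- All four liquid days: 50 × 4 = 200. Both tumor days: 50 × 2 = 100. The additional 100 liquid samples and 50 tumor biopsies, from days 28 and 42, are uncertain only in nivolumab dose count.

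**Does another passage settle the order?** Sections 8.2, 8.7.5 and 8.7.6 and Table 4 contain no requirement to sample before the infusion. Section 8.7.6 says only that an attempt is made to combine research blood with the routine draw. The routine draw is itself a same-visit procedure under 8.7.1, so its order is open too. If a visit is split so that sample and infusion fall on different dates, the dates show the order; the ambiguity concerns samples taken on the same date as the infusion.

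**After the change.** If samples always precede the infusion, each day has one exposure state: CRT only at day 7; one ipilimumab dose added by day 14; one nivolumab dose added by day 28; a second by day 42. The day 7 to 14 change in blood would then follow ipilimumab alone, on top of continuing CRT, with controls sampled at the same visits as reference.

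**The case against.** The strongest reply is that section 8.7.1 permits mixing but does not cause it. Sites may well draw research blood with the routine bloods before the infusion. That stands: the counts above are upper bounds, and the documents do not show how many samples would be affected.

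It can also be said that a required date does not forbid recording a time. The eCRF is not shown, section 9.6 already asks for date and time of adverse events, and laboratory reports are kept as source documents. This also stands in part. Some times may be recoverable, but nothing in section 8.7.1 ensures it.

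Figure 1 is not shown and might indicate an order. If it does, it needs reconciling with the explicit statement in 8.7.1 that none applies.

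Three stronger readings are tempting and are not supported.

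- A reader might infer that the trial cannot separate ipilimumab from nivolumab effects because of this rule. Separating the two drugs is not a stated objective, and there is no single-drug arm. At days 28 and 42 order makes no difference to whether both drugs have been given. A day 14 sample taken after the infusion carries only same-day nivolumab exposure, against 14 − 7 = 7 days since ipilimumab. Attribution is weakened, not ruled out.
- A reader might infer that the arm comparison is invalid. It is not. Table 4 restricts only visits 9 and 10 to the treatment arm, so controls are sampled on the same days without immunotherapy. Variable timing adds noise to the combination-versus-CRT contrast but does not remove it.
- A reader might infer a conflict with section 8.2.5, which says: "The Investigator must temporarily interrupt or permanently discontinue the study drug according to the specifications in the drug specific SmPC". The two passages do not contradict each other. Sections 8.2.5 and 8.2.9 defer to the SmPC, and the scheduling rule in 8.7.1 overrides neither.

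**Conclusion.** The point holds as a limited design weakness in the secondary biomarker work. As written, the plan allows treatment-arm samples with one day label to represent two exposure states, and its minimum record cannot distinguish them when sample and infusion share a date. The consequence is avoidable noise in the longitudinal and between-arm biomarker analyses, with most effect at days 7 and 14: at most 100 liquid samples and 50 tumor biopsies. At days 28 and 42 only the nivolumab dose count is uncertain. The primary safety endpoint and its decision rules are untouched.

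This assumes that all 50 treatment-arm patients attend and are sampled and infused on the scheduled days, and that no order is fixed in a figure or site document not available here. The share of samples actually taken after the infusion could lie anywhere from none to all. A uniform habit at either extreme would give consistent states; mixed habits are what do the harm. The change is worth making because it is cheap and because the day 14 and 28 tumor biopsies are additional study-specific procedures.

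**What to change.** In section 8.7.1, add an exception to the no-sequence rule for visits 3, 4, 6 and 8: research blood and tumor samples are collected before that day's infusion. Record in the eCRF the clock time of each such sample and of the infusion start. Keep samples taken after infusion start, flag them, and handle them in a sensitivity analysis; excluding them would waste invasive biopsies without need.

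Stool samples and the quality-of-life questionnaire need not be brought under the rule, since nothing in the documents shows that a same-day infusion would alter them.

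The cost is one sentence in 8.7.1, time fields in the eCRF, and slightly less scheduling freedom on infusion days. No visit or sample is added.

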### 8.7.2 Screening investigation

Screening investigations will be done according to standard routine surgical practice for patients with rectal cancer who need a neoadjuvant CRT [3].

### 8.7.3 Assessment of safety and tolerability

Safety, tolerability and feasibility assessed by the latest “Clavien-Dindo Classification of surgical complications” [26] (see section 9.1.2) and CTCAE [27] (see section 9.4).

### 8.7.4 Laboratory tests

Laboratory test and procedures will be done according to standard clinical practice for patients with rectal cancer who receive a neoadjuvant CRT following surgical resection [3].

- Blood count:

[figure not shown]

- Erythrocytes
  - Hemoglobin
  - Thrombocytes
  - Leucocytes
    - Neutrophils
    - Lymphocytes
    - Monocytes
    - Eosinophils
    - Basophils
- Coagulation:
  - Thromboplastin time (PTZ)
  - International normalized ratio (INR)
  - Partial thromboplastin time (aPPT)
- Kidney:
  - Creatinine
  - Blood urea nitrogen (BUN)
- Liver/Pancreas
  - Aspartate aminotransferase (ASAT) / Glutamic oxaloacetic transaminase (GOT)
  - Alanine aminotransferase (ALAT) / Glutamate-pyruvate transaminase (GPT)
  - Gamma-glutamyltransferase (Gamma-GT)
  - Alkaline phosphatase (AP)
  - Bilirubin
  - Pancreatic amylase
  - Lipase
  - Lactate dehydrogenase (LDH)
- Protein diagnostic
  - Albumin
- Inflammation
  - C-reactive protein (CRP)
- Glucose metabolism
  - Glucose
  - Glycated hemoglobin (HbA1c)
- Thyroid diagnostic
  - Thyroid-stimulating hormone (TSH)
  - Free thyroxine (fT4)
  - Free triiodothyronine (fT3)
- Cardiac diagnostic
  - Troponin T (TnT)
  - Creatine kinase (CK)
  - Creatine kinase muscle-brain (CK-MB)
  - NT pro brain natriuretic peptide (proBNP)
- Hormones
  - Beta-human chorionic gonadotropin (beta-hCG)
- Tumor marker
  - Carcinoembryonic antigen (CEA)
  - Carbohydrate antigen 19-9 (CA 19-9)

### 8.7.5 Tumor biopsies

Additional biobanking will be done from pretherapeutic biopsies (day -21 to -1), which are collected anyhow for routing clinical diagnostic, as well as from tumor resected specimen (between week 15 to 17). Additional study specific interventions would include tumor biopsies on day 14 and 28. Tissue biobanking material will be used for genomic, transcriptomic, epigenomic and/or proteomic investigations/correlations with therapy response and clinical outcome.

Genomic analysis of circulating tumor DNA (ctDNA) and tumor tissue DNA will include standard high throughput next generation sequencing (NGS) technologies, such as whole genome sequencing (WGS) and/or whole exome sequencing (WES).

Transcriptomic analysis will include standard high-throughput technologies, such as single-cell RNA sequencing (scRNA-seq), single-cell T-cell receptor sequencing (scTCR-seq), single-cell B-cell receptor sequencing (scBCR-seq), single nuclei RNA sequencing (snRNA-seq), spatial transcriptomics (Visium Spatial platform, 10X Genomics), cellular indexing of transcriptomes and epitopes by sequencing (CITE-seq) [35] and/or RNA expression and protein sequencing assay (REAP-seq) [36].

Epigenomic analysis will include reduced representation bisulfite sequencing (RRBS) [37] and/or chromatin immunoprecipitation DNA-sequencing (ChIP-seq) [38]–[40].

Proteomic and metabolomic will include standard high-throughput technologies, such as orbitrap mass spectrometry, matrix assisted laser desorption/ionization (MALDI), electrospray ionization (ESI), liquid chromatography–mass spectrometry (LC–MS), gas chromatography–mass spectrometry (GC–MS) and/or cytometry by time of flight (CyTOF) [41]. Protein analysis of single cell suspensions will include standardized flow cytometry (FCM) techniques. Tissue protein analysis will include standard immunohistochemistry (IHC) and/or multiplex immunofluorescence assays (*i.e.* Akoya Biosciences). Stained tissue sections will be quantified by whole-slide tissue scanning systems (*i.e.* Vectra Polaris, PerkinElmer) and further analyzed with an image analysis software (*i.e.* HALO, Indica Labs).

All multi-omic analysis will be assessed longitudinal for intra/inter tumor heterogeneity and further correlated with therapy response and clinical outcome. Moreover, samples will be compared between the 2 different patient groups (control arm vs. treatment arm).

All analysis will be only done by or in cooperation with local and/or international non-profit/non-commercial academic centers, such as universities or research institutions. *i.e.* VIB KU Leuven Center for Cancer Biology ([name]), Research Center for Molecular Medicine (CeMM) of the Austrian Academy of Sciences ([name]), Joint Microbiome Facility (JMF) of the Medical University of Vienna and the University of Vienna ([name]) and/or members of the Society for Immunotherapy of Cancer (SITC).

### 8.7.6 Liquid biopsies

Study specific interventions include biobanking of liquid biopsies (serum, plasma, PBMCs) on day -21 to -1, 7, 14, 28, 42, before surgery and at the EOSV. Blood samples are tried to be collected during routine blood drawing. Biobanking material (blood and tissue) will be used for genomic, transcriptomic, epigenomic and/or proteomic investigations/correlations with therapy response and clinical outcome.

Analysis of longitudinal liquid biopsies will be analyzed according to the above-mentioned tumor tissue biopsies.

### 8.7.7 Stool biobanking

Additional stool biobanking will be done concomitant with the tumor biopsy interventions described above in section 8.7.5 Stool biobanking material will be used for metagenomics, metatranscriptomics,

[figure not shown]

metaproteomics and/or metabolomics investigations/correlations with therapy response and clinical outcome.

Metagenomic analysis will include high-throughput technologies, such as highly multiplexed gene amplicon sequencing (*i.e.* 16S rRNA genes).

Metatranscriptomics will be done by high-throughput technologies, such as Illumina HiSeq-/NovaSeq.

Metabolomics will be analyzed by LC-MS, GC-MS and/or nuclear magnetic resonance (NMR) spectroscopy.

Analysis of longitudinal meta-omics data will be complemented with functional assays, such as bacterial cultivation of harvested stool samples/swabs and further correlated with therapy response and clinical outcome. Moreover, samples will be compared between the 2 different patient groups (control arm vs. treatment arm).

### 8.7.8 End-of-study (EOS) examination

After successful surgery (approximately 20 weeks after treatment period) patients undergo the EOS examination, which entails a standard patient visit according to routine surgical practice.

### 8.7.9 Definition of the end of the trial

The end of the trial is defined as the date of the last visit of the last patient undergoing the trial.

[figure not shown]

## 9 SAFETY DEFINITIONS AND REPORTING REQUIREMENTS

### 9.1 Surgical complications

#### 9.1.1 Definitions

Surgical complications are defined as any deviation from the normal postoperative course. This definition also considers asymptomatic complications such as arrhythmia and atelectasis.

A sequela is an “after-effect” of surgery that is inherent to the procedure (*i.e.* inability to walk after an amputation of the leg).

Finally, surgery may be well executed without any complications but still fail. If the original purpose of surgery has not been achieved, this is not a complication but a “failure to cure” (*i.e.* residual tumor after surgery). Sequelae and failure to cure should not be included in the new classification of complications.

#### 9.1.2 Severity of surgical complications

Surgical complications will be assessed and graded according to the latest “Clavien-Dindo Classification of surgical complications” [26]. Briefly, it consists of 7 grades (I, II, IIIa, IIIb, IVa, IVb and V). Subclasses a and b can be omitted to contract the classification into 5 grades (I, II, III, IV and V), depending on the size of the population and/or the of the emphasis of a study.

##### **Grade I**

Any deviation from the normal postoperative course without the need for pharmacological treatment or surgical, endoscopic and radiological interventions. Allowed therapeutic regimens are: drugs as antiemetics, antipyretics, analgetics, diuretics and electrolytes and physiotherapy. This grade also includes wound infections opened at the bedside.

##### **Grade II**

Requiring pharmacological treatment with drugs other than such allowed for grade I complications. Blood transfusions and total parenteral nutrition are also included.

##### **Grade III**

Requiring surgical, endoscopic or radiological intervention

